### Participant identification and consent

The recruitment plan is twofold: 1) Open recruitment for people with MS through MS Irelands communication channels for two months duration. This will employ the same procedures as that of our published protocol for a previous qualitative study (
[name] *et al*., 2019). A co-investigator (HD) will send recruitment letters (Appendix A, extended data (
[name], 2020)), study information sheets, and screening forms (Appendix B, extended data (
[name], 2020)) to a gatekeeper at MS Ireland who will send the emails to all people with MS and who will place the study notifications on their social medial channels. 2) In addition, our recruitment strategy will include a convenience sample of people with MS from an existing cohort of people with MS who have already participated in a qualitative telephone interview study of urinary problems. The protocol for that study, including recruitment strategies, are described in detail elsewhere (
[name] *et al*., 2019).

Interested and eligible participants will be invited to contact a member of the research team including the principal investigator (KR) or co-investigators (SC) or (HD) using the contact methods provided in the email. Once a participant contacts any member in the research team, a call will be arranged via MS Ireland’s Zoom for Healthcare account with (HD) to review eligibility and provide details of the full procedure of the study including the protocol of the nerve stimulation intervention and the outcome measures and give prospective participants the opportunity to ask questions. Participants will be made aware that they have the full right to withdraw at any stage without any explanation. Those who elect to participate will be provided with the link via email to a survey hosted on
Qualtrics Survey Software to read and sign the informed consent form, complete demographic data (Appendix C, extended data (
[name], 2020)) including the Patient Determined Disease Steps (PDDS) (
Learmonth *et al*., 2013), the International Consultation of Incontinence Questionnaire-Overactive bladder (ICIQ-OAB), King’s Health Questionnaire, the 3- day bladder diary (Appendix D, extended data (
[name], 2020)) , adverse events report diary (Appendix E, extended data (
[name], 2020)), and adherence to treatment protocol (Appendix F, extended data (
[name], 2020)). The 3-day bladder diary, ICIQ-OAB, and King’s Health Questionnaire are to be filled twice during the study; at base line before commencing the intervention (week 0) and post commencing the intervention at the end of (week 6). Diaries including adverse events report diary and adherence to treatment protocol diary are to be filled throughout the study from (week 0) till the end of (week 6) to document any observation related to the application of the intervention. The Questionnaire for Acceptability (Appendix G, extended data (
[name], 2020)) is to be filled at the end of the intervention at the end of (week 6) to allow the researcher to determine the participant’s satisfaction level with application of TTNS.

Once participants provide the signed consent form and complete the required outcome measures, a call will be arranged using MS Ireland Zoom Healthcare account to provide details in how to apply the nerve stimulation and allow an opportunity to ask questions. After the call, all participants will be emailed a short video showing the nerve stimulation application as a reminder in how to apply the TENS unit.

The nerve stimulation unit will be posted to them by an MS Ireland’s staff member. In this package, a stamped addressed envelope will also be provided to facilitate return of the nerve stimulation unit.

During the Zoom video call participants will be given an option for paper copy of diaries instead of downloadable documents via Qualtrics Survey Software. In this scenario, HD will inform the interested participants that the hard copies of the diaries will be posted with the TENS unit.

Participants will be called by HD on a weekly basis using MS Ireland Zoom Healthcare account to check adherence to treatment protocol, any reported adverse event, discuss any issues raised up by participants, and at the end of the study will remind them to complete the outcome measures. Responses from participants will be documented to be cross-checked against the self- reported diaries for adherence and adverse events. The study will be discontinued for individual participants if participants report an adverse reaction to the application or use of TTNS.

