## Abstract

**Background:** Neurogenic lower urinary tract dysfunction (NLUTD) is common among people with multiple sclerosis (MS) with a pooled prevalence of 68.41% using self-report measures and 63.95% using urodynamic studies. Transcutaneous tibial nerve stimulation (TTNS) is a non-invasive option to manage bladder storage symptoms; however, the potential efficacy of TTNS among people with MS is based on a small number of studies with the absence of high-quality evidence relating to efficacy, and lack of clarity of the optimal electrical stimulation parameters and frequency, duration and number of treatment sessions. This study aims to assess whether TTNS is feasible and acceptable as a treatment for bladder storage symptoms in people with MS.

**Methods:** We will use a single-arm experimental study to explore the feasibility and acceptability of TTNS in the treatment of bladder storage symptoms in MS. The CONSORT extension for pilot and feasibility studies will be followed to standardise the conduct and reporting of the study. The recruitment plan is twofold: 1) Open recruitment for people with MS through MS Ireland’s communication channels; 2) recruitment from a convenience sample of people with MS who have previously participated in a qualitative interview study of urinary symptoms. We will assess recruitment/retention rates, the urinary symptoms changes and the effect on quality of life pre and post intervention using ICIQ-OAB, 3-day bladder diary, King’s Health Questionnaire and collect self-reported data on adherence and adverse events. Acceptability of using TTNS will be evaluated at the end of intervention. This study has been reviewed and approved by the Education and Health Science’s Faculty Research Ethics Committee, University of Limerick [2020_06_07_EHS].

**Conclusion: **It is anticipated that assessing the feasibility and acceptability of TTNS for storage bladder symptoms in MS will inform the development of a definitive randomised trial.

**Trial registration**: ClinicalTrials.gov
NCT04528784
****27/08/2020

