### Specific objectives

The overreaching aim of this study is to assess whether transcutaneous tibial nerve stimulation (TTNS) is feasible as a treatment for bladder storage symptoms in people with MS. In particular, the study will explore the feasibility and acceptability of TTNS application in people with MS by addressing the following specific objectives:

*The primary objectives are* to a) assess the recruitment and retention rates, b) investigate the completion rate and appropriateness of outcome measures by participants; c) assess safety by reporting the number of participants with adverse events; d) determine participants’ adherence to the treatment protocol, and e) assess participant’s satisfaction with TTNS application.

*The secondary objectives are to* a) evaluate the preliminary effectiveness of TTNS in managing bladder storage symptoms in MS; and to b) determine the effect of TTNS on quality of life in people with MS.

Addressing these objectives will establish a foundation for future definitive randomised trial to explore the efficacy of TTNS on bladder storage symptoms in MS.

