### Outcomes

**Primary outcome measures**. A) Feasibility will be assessed by the proportion of participants who: are recruited to the study, complete assigned outcome measures, complete the 6-week intervention, and are lost to follow up. Also, feasibility will be assessed by the overall level of adherence achieved over the study period of 6-weeks through the self-report diary (
Anghel *et al*., 2019). Adverse events will be measured using a self-report diary and will include (but will not be limited to) any device related skin redness at the site of stimulation, discomfort at the stimulation site that might persist post treatment session. B) Acceptability (satisfaction) of TTNS application will be assessed using a self-report questionnaire developed by the researchers containing 5-point Likert scales: 1= “strongly disagree”; 2= “disagree”; 3= “neutral”; 4= “agree”; 5= “strongly agree”.

**Secondary outcome measures** include the followings:

The storage symptoms will be assessed by ICIQ-OAB (
Abrams *et al*., 2018;
Zappavigna & Carr, 2015). It has grade A for validity, reliability and responsiveness to change established with rigour on one data set. The total score ranges from 0 to 16 with higher values indicating increased symptom severity. Bother scales are not incorporated in the overall score (
Abrams *et al*., 2006).Severity of frequency, nocturia, and incontinence will be assessed by using a standard 3-day bladder diary (
Jimenez-Cidre *et al*., 2015;
Nambiar & Lucas, 2014). Number of episodes of frequency, nocturia, and incontinence/ 72 hours will be calculated and compared from baseline with higher values indicating increased symptom severity.Severity and intensity of urgency will be assessed using Patient Perception of Intensity of Urgency Scale (PPIUS) (
Notte *et al*., 2012). Number of urgency episodes and severity of urgency/72 hours will be calculated and compared from baseline. The total score ranges from 0 to 4 with higher values indicating increased symptom severity.Quality of Life (QoL) will be evaluated by using King’s Health Questionnaire (
Nambiar & Lucas, 2014;
Okamura *et al*., 2009;
Pat Ray *et al*., 2003). A change from baseline of 5 points or higher on most of the King’s Health Questionnaire domains represents a clinically meaningful improvement in health-related quality of life after treatment (
Kelleher *et al*., 2004).

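### The acceptability questionnaire is scheduled only at the end of week 6, so participants who withdraw earlier give no satisfaction rating and the primary acceptability estimate is likely, though not certainly, too favourable

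*Protocol article*

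**What the plan says.** Satisfaction has primary status twice. Under Specific objectives, the last primary objective is to "assess participant’s satisfaction with TTNS application". Under Outcomes, primary outcome B reads "Acceptability (satisfaction) of TTNS application will be assessed using a self-report questionnaire developed by the researchers", scored on 5-point Likert scales.

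The timing is also stated twice. Participant identification and consent says that the questionnaire "is to be filled at the end of the intervention at the end of (week 6"); its stated purpose there is to measure how satisfied participants are. The Abstract agrees: "Acceptability of using TTNS will be evaluated at the end of intervention".

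The same consent section allows for early exit. Participants are told that "they have the full right to withdraw at any stage without any explanation". It also states: "The study will be discontinued for individual participants if participants report an adverse reaction to the application or use of TTNS". Neither sentence is linked to a satisfaction rating at exit, and no other section schedules one.

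Three further provisions matter:

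- Weekly calls cover adherence, adverse events and any issues that participants bring up, and the responses are documented. The reminder to complete outcome measures comes at the end of the study.
- Adherence and adverse-event diaries run from week 0 to week 6.
- Under Outcomes, completion of the intervention, completion of outcome measures and loss to follow-up are themselves primary feasibility results.

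**The concern.** Whether a person reaches the only scheduled rating may depend on what the rating measures. The treatment is self-applied at home for 30 minutes, three times a week for six weeks. Burden, difficulty placing the electrodes or lack of perceived benefit are plausible reasons to leave. If those who leave for such reasons are missing, the satisfaction figure describes mainly the people content to stay.

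The result is meant to inform a definitive randomised trial. With about 20 participants, each missing person is 1/20 = 5 percentage points of the total, so a few exits can change how acceptable the treatment appears. A rating that was not collected at exit cannot be recovered by any later analysis.

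**Working it through.** **Figures in the plan.** There is none to reproduce. The 20 under Sample size is an anticipated number without a formula, and the article gives no expected dropout or satisfaction rate. The check is therefore a reading of the schedule, followed by an illustration.

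**Step 1: who reaches the rating, as the schedule is written?**

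| Participant | Rating scheduled? |
|---|---|
| Completes six weeks | Yes, end of week 6 |
| Stops stimulation, stays enrolled | Yes, end of week 6; nothing restricts it to completers |
| Withdraws from the study before week 6 | None stated |
| Study discontinued after a reported adverse reaction | None stated |

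The gap is the last two rows. The point does not depend on the adverse-reaction rule, on which no view is taken here.

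**Step 2: formula.** Let N be the number recruited, k the number who leave without a rating, p_r the proportion satisfied among respondents and p_l the proportion among leavers. Then

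respondents' figure − figure for all = p_r − [(N − k)·p_r + k·p_l]/N = (k/N)·(p_r − p_l).

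The difference is zero if nobody leaves or if leavers are as satisfied as respondents. It is negative if leavers are more satisfied.

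**Step 3: worked example.** N = 20 is from Sample size. Assumed: k = 4, and 14 of the 16 respondents satisfied. The respondents' figure is 14/16 = 87.5% (exact 95% CI 61.7 to 98.4).

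| Leavers satisfied (of 4) | Figure for all 20 | Respondents minus all |
|---|---|---|
| 0 | 14/20 = 70% | +17.5 points |
| 1 | 15/20 = 75% | +12.5 points |
| 2 | 16/20 = 80% | +7.5 points |
| 3 | 17/20 = 85% | +2.5 points |
| 4 | 18/20 = 90% | −2.5 points |

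The exact 95% CI is 45.7 to 88.1 for 14/20 and 68.3 to 98.8 for 18/20.

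**Step 4: sensitivity to the number leaving.** Assumed: p_r = 90%, N = 20. Entries are respondents minus all, in percentage points.

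| k | p_l = 0% | p_l = 25% | p_l = 50% | p_l = 90% |
|---|---|---|---|---|
| 2 | 9.0 | 6.5 | 4.0 | 0 |
| 4 | 18.0 | 13.0 | 8.0 | 0 |
| 6 | 27.0 | 19.5 | 12.0 | 0 |

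For example, k = 4 and p_l = 50% give (4/20)·(0.90 − 0.50) = 0.08.

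**The case against.** A reader might infer that everyone who stops early goes unasked. The article does not say that. It sets a date and does not limit the questionnaire to those who complete treatment, so a person who stops stimulation in week 3 but remains enrolled is still due it at week 6. This objection stands, and it narrows the point to people who leave the study.

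A reader might also infer that complaints and reasons for stopping are not captured at all. That goes too far. The weekly calls are documented and open to any issue that a participant raises, and the diaries take observations on applying the device. These may record some reasons, though no reason-for-stopping item is described. They do not supply the Likert ratings that define outcome B.

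Attrition is reported as a primary outcome, so readers will see how many ratings could be missing. That makes the gap visible but does not show what the missing people thought.

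The Statistical methods section fixes neither a denominator for satisfaction nor a cut-off for being satisfied. The 87.5% is therefore what respondents would show, not a figure that the plan commits to. Such choices can properly sit in an analysis plan and are not criticised here.

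Finally, the article is condensed, and Data management and confidentiality refers to a full protocol in a repository that is not shown. An exit procedure may exist there. Even so, the article states the timing positively, in two places, and both point to the end of the intervention. The consent section equates that with week 6, which leaves little room to read it as each person's own stopping date.

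**Conclusion.** The point holds in a limited form. Followed as written, the schedule collects no satisfaction rating, for a primary outcome, from participants who leave the study before the end of week 6.

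The likely direction of bias is upward, because dissatisfaction is a plausible reason to leave. It is not certain: people also leave for unrelated reasons, and the documents do not support calling the estimate biased by design. In the example the respondents' 87.5% compares with 70% to 90% for all 20, that is, from 17.5 points too high to 2.5 points too low. The number leaving and both satisfaction rates are assumptions, and the sampling uncertainty with 16 respondents is itself wide.

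This is a cheap improvement rather than a fault that undermines the study.

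**What to change.** Change the schedule sentence so that the Questionnaire for Acceptability is offered at the end of week 6 or at early withdrawal, whichever comes first. Send it through the Qualtrics system already in use, with an optional item on the reason for stopping. Bring the Abstract's statement of timing into line.

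In reporting:

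- give satisfaction for all who used TTNS and answered;
- show early-exit ratings separately from week 6 ratings;
- give the result with non-responding leavers counted as not satisfied only as a lower bound, since it understates acceptability when people leave for unrelated reasons.

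The cost is one sentence and one survey link. Both the exit questionnaire and the reason item must stay optional, so that the right to withdraw without explanation is kept. No treatment rule changes. The small downside is that some ratings will reflect fewer than six weeks of use, which the separate display handles.

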### TTNS Intervention: 

**Type of equipment**: Stimulation of posterior tibial nerve will be delivered by Transcutaneous Electrical Nerve Stimulation (TENS) unit.
**Application of TTNS:** based on the anatomical distribution and previous reports: the anode will be positioned between 5–10 cm above medial malleolus and posterior to the edge of the tibia and the cathode will be positioned distally on arch of the foot (
Castel-Lacanal, 2015;
Mcguire *et al*., 1983). The accurate location of electrode is considered by contractions of the appropriate muscles innervated by posterior tibial nerve; sensory response by tingling sensation of sole of the foot and / or motor response by flextion of big toe and fanning of the other toes.
**Patient position**: participant will be advised to lie supine with extended legs or supported sitting with knee extension in order to allow the nerve roots to be free from any compression at knee joint.

Participants will be advised to ensure that their skin is clean skin under the electrode to minimize skin resistance. In cases where participants apply skin mosturiser, they will be advised to wipe the area with alcohol swap or with soap and water and ensure the area is completely dry prior to electrodes application.

**Duration of Treatment:** A six weeks intervention period has been shown to be effective among a neurogenic population (
Monteiro *et al*., 2014) and preferable among participants who has been interviewed during phase II study
*(
[name] et al., 2019)*

**Side of Lower leg**: based on physiology of the central nervous system control of the bladder we would use the left ankle for the application of TTNS because it has been shown that the right side of the brain is the predominant active area in micturition (
de Groat, 1997;
Sand & Sand, 2013).
**Frequency:** 10 HZ. It has been shown that low frequency of 10HZ is effective in inhibiting sympathetic nervous system that might normalize bladder functions (
Robertson *et al*., 2006).
**Intensity:** the intensity of stimulation will be at the sensory and motor threshold by tingling sensation on sole of the foot with flexion of big toe and /or fanning of other toes. The stimulation should not be painful (
Zecca *et al*., 2014).
**Pulse duration**: 200 microseconds, it is important to be long enough to allow action potentials to leave the hyperpolarization zone induced by anodic phase (
Vargas Luna *et al*., 2017). It is consistent with previous studies.

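### As narrated, participants are taught TTNS before the TENS unit is posted, and no described step has staff check placement or response afterwards, so diary adherence may count sessions done rather than sessions delivered as specified

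*Protocol article*

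**What the plan says.** The protocol article, under *Participant identification and consent*, describes the start of treatment in sequence. Once consent and baseline measures are complete, "a call will be arranged using MS Ireland Zoom Healthcare account to provide details in how to apply the nerve stimulation". Next, "After the call, all participants will be emailed a short video showing the nerve stimulation application as a reminder". The following paragraph adds: "The nerve stimulation unit will be posted to them by an MS Ireland’s staff member". The article then says that, during the Zoom video call, participants may choose paper diaries and are told that these will go in the same post as the unit.

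Under *TTNS Intervention*, correct location is recognised by what the stimulation produces: "The accurate location of electrode is considered by contractions of the appropriate muscles innervated by posterior tibial nerve", which the text expands as "sensory response by tingling sensation of sole of the foot and / or motor response by flextion of big toe and fanning of the other toes". Intensity is set by the same signs, at the sensory and motor threshold. Treatment is self-administered at home (*Setting*), three times a week for six weeks.

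After delivery, a co-investigator calls each participant weekly on Zoom. The calls check adherence to the treatment protocol, ask about adverse events and discuss issues that participants raise. The answers are compared with the self-report diaries. Under *Outcomes*, adherence is a primary feasibility measure taken from the self-report diary.

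**The concern.** The evoked response is how the participant knows that the electrodes are in the right place and the current is high enough. It cannot be produced, seen or asked about on a call held without the device. If the teaching call comes before the unit arrives, the first real application is made alone at home, and no later step is described in which staff confirm it.

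The study asks whether self-applied TTNS is feasible, as groundwork for a definitive randomised trial. One objective is adherence to the treatment protocol, and that protocol includes electrode site and response-based intensity. Suppose diary adherence is high and symptoms change little. Without a check on delivery, the study could not say whether the treatment did little or was not delivered as specified. It would also miss a useful feasibility result: how many people reach the required response after remote teaching.

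**Working it through.** The plan states no figure to reproduce. No sample size was calculated, and 20 is the anticipated number. The check is of the order of steps, followed by simple arithmetic for scale.

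**1. Order of the steps, as narrated**

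| Step | Protocol article | What it establishes |
|---|---|---|
| Trigger | "Once participants provide the signed consent form and complete the required outcome measures, a call will be arranged" | The teaching call follows baseline |
| Content of the call | "to provide details in how to apply the nerve stimulation and allow an opportunity to ask questions" | Explanation and questions; no supervised application is described |
| Next | Reminder video by email | One-way; nothing is observed |
| Next | Unit posted by MS Ireland staff | Described after the call and video, without a date |
| During the Zoom video call | Paper diaries to be posted with the unit | At that call the unit has not yet been sent |

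The narrative puts teaching before posting. The last row supports this only if the call meant is the teaching call. The article describes two Zoom calls before treatment, the other being the eligibility call, and does not say which is meant.

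**2. Later contacts**

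The weekly calls take place with the unit in hand, but their described content is questions and answers. The cross-check compares one self-report with another. It can catch a forgotten or misreported session. It cannot catch a wrong placement or a setting below threshold that the participant believes to be correct.

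**3. Scale**

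Inputs from the document: 20 participants (*Sample size*); 3 sessions a week for 6 weeks (*TTNS Intervention*).

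- Sessions per participant: 3 × 6 = 18
- Planned sessions: 20 × 18 = 360

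Assumptions, none from the document: a proportion m of participants misdeliver all 18 sessions; recorded adherence is 90% and the same in those who misdeliver and those who do not.

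- Planned sessions affected = 360 × m
- Recorded sessions that were misdelivered = 0.90 × 360 × m
- Share of planned sessions correctly delivered = 0.90 × (1 − m)

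| Assumed m | Participants | Planned sessions affected | Recorded but misdelivered | Correctly delivered |
|---|---|---|---|---|
| 10% | 2 | 36 | 0.90 × 36 ≈ 32 | 0.90 × 0.90 = 81% |
| 30% | 6 | 108 | 0.90 × 108 ≈ 97 | 0.90 × 0.70 = 63% |

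At m = 10%, the chance that at least one of 20 participants is affected is 1 − 0.90^20 = 88%. Even at m = 5% it is 1 − 0.95^20 = 64%.

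**The case against.** A reader might infer that nobody ever sees the response and that misdelivered sessions are counted as adherence. The documents do not support either statement, for these reasons.

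- **The order is not fixed.** No sentence dates the posting relative to the teaching call. The teaching call follows completion of the baseline measures, which include the 3-day bladder diary. If the paper option covers that diary, it must be offered at the eligibility call, and the package holding the unit could arrive before teaching. If it covers only the adherence and adverse-event diaries, the narrated order stands. This objection holds to the extent that the order is a strong inference and not a stated fact.
- **Participants can check themselves.** They feel the tingling and can see their own toes. Tingling of the sole also counts for location, so toe movement is not the sole criterion, and tingling cannot be seen by an observer. This stands. What is missing from the description is a check by staff.
- **The adherence diary is not shown.** It is an appendix in the extended data, and the diaries are also meant to capture observations about applying the treatment. The weekly calls refer to the treatment protocol, which could be read to include placement and intensity. This stands, so the most that can be said is that the diary may count such sessions. A response recorded only by the participant would still be unverified.
- **The article is condensed.** Training detail may lie in the full protocol. This stands in part: the absence of a check here does not prove that none exists. But the article does set out teaching and posting in sequence, and the point is about that sequence.
- **Effectiveness is secondary, and the study is small and uncontrolled.** This is true, and symptom change will be hard to interpret in any case. The argument from feasibility and adherence does not depend on it.

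**Conclusion.** The point holds in a limited form. As narrated, teaching precedes posting, and no described step has staff check placement or the sensory or motor response once the participant has the unit. An error that the participant does not recognise could therefore persist, and diary adherence may measure sessions done rather than sessions delivered as specified.

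The size is unknown. The fall from 90% to between 81% and 63% illustrates the possible effect and is not an estimate. It rests on an assumed misdelivery rate, an assumed diary adherence, and errors that last all 18 sessions despite weekly contact; errors corrected early would give a smaller loss. The change is worth making because it is cheap and bears directly on what this feasibility study is meant to show.

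**What to change.** Use the calls already planned, in a different order:

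1. Post the unit, with any paper diaries, before the teaching call, and ask participants not to use it until then.
2. Have the participant apply it on camera during the teaching call.
3. Record the electrode site and the response obtained: toe movement as seen by staff, tingling as reported by the participant.
4. Report the number of participants who reach the response described under *TTNS Intervention* as a descriptive feasibility outcome.
5. Repeat the check briefly in one planned weekly call.

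At the least, the article should state when the unit arrives relative to the teaching call, whether staff verify the response, and what the adherence diary records.

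The cost is a longer teaching call and a few days' wait for the post. The participant also holds the device for a short time before being taught, hence the request in step 1. No stimulation setting, schedule or counting of treatment days is changed.

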### Sample size

This is a pilot study and a formal sample size is not computed. We anticipate that a total of 20 participants will be recruited to the pilot study within two months.

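### Read literally, an adverse reaction ends the study and not only stimulation for that participant, leaving no scheduled point for acceptability and week-6 outcome data

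*Protocol article*

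**What the plan says.** All places are in the protocol article.

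- **Stopping rule** (Participant identification and consent): "The study will be discontinued for individual participants if participants report an adverse reaction to the application or use of TTNS". It has no severity qualifier and does not say whether data collection continues.
- **Acceptability questionnaire** (same section): it "is to be filled at the end of the intervention at the end of (week 6"). No other time is given.
- **Symptom and quality-of-life measures** (same section): the bladder diary, ICIQ-OAB and King's Health Questionnaire "are to be filled twice during the study; at base line before commencing the intervention (week 0"), and then at the end of week 6.
- **Prompt** (same section): the weekly caller "at the end of the study will remind them to complete the outcome measures". No other prompt for the post-baseline measures is described.
- **Primary objectives** (Specific objectives): these include to "assess the recruitment and retention rates", and also cover completion of outcome measures, adverse events, adherence and satisfaction.
- **Feasibility outcomes** (Outcomes): the proportions who "complete assigned outcome measures, complete the 6-week intervention, and are lost to follow up" are listed as separate items.
- **Adverse events** (Outcomes): examples are "any device related skin redness at the site of stimulation, discomfort at the stimulation site that might persist post treatment session".
- **Sample size**: "We anticipate that a total of 20 participants will be recruited to the pilot study within two months".

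**The concern.** Stopping a treatment and stopping data collection are different acts, and the Outcomes section keeps them apart by listing completion of measures, completion of the intervention and loss to follow-up separately. The stopping rule, as worded, merges them. A participant who reacts in week 2 and would gladly go on answering questionnaires is, on the literal text, out of the study four weeks before the only post-baseline assessment.

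Two things are at stake, both within the primary objectives. First, outcome-measure completion would fall because of the rule and not because follow-up proved infeasible, so it would mislead as a planning figure for the definitive trial. Secondly, satisfaction would be summarised mainly in people who had no reaction. Those who tolerated the device worst, whose views on acceptability matter most, would be left out, and the summary would probably look too favourable.

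**Working it through.** The plan gives no figure to reproduce: there is no formal sample size, no expected reaction rate and no retention target. The check therefore has two parts, the text and an illustration of scale.

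**Text.** Suppose a participant reports a reaction in week *w*, with *w* < 6.

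1. Under the stopping rule, the study ends for that participant in week *w*.
2. The acceptability questionnaire and the second set of outcome measures fall due at the end of week 6.
3. The reminder comes at the end of the study. No early-stop assessment or later follow-up is described.
4. Literally, then, no scheduled point remains for these data. Steps 1 to 3 are stated; step 4 is an inference.

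**Ceiling on completion.** Inputs: n = 20 (Sample size); k = number stopped after a reaction, **assumed** to be 1, 2 or 4. The highest possible outcome-measure completion under the literal wording is (20 − k)/20. The same ceiling applies to retention if that means remaining under follow-up. The plan promises 95% intervals, so exact (Clopper–Pearson) limits are shown: with x = 20 − k, the lower limit is the 2.5% quantile of Beta(x, n − x + 1) and the upper limit is the 97.5% quantile of Beta(x + 1, n − x).

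| k | Literal wording: ceiling (exact 95% CI) | Stimulation only stopped: ceiling (exact 95% CI) | 6-week intervention completed, either wording |
|---|---|---|---|
| 1 | 19/20 = 95% (75.1–99.9%) | 20/20 = 100% (83.2–100%) | at most 95% |
| 2 | 18/20 = 90% (68.3–98.8%) | 20/20 = 100% (83.2–100%) | at most 90% |
| 4 | 16/20 = 80% (56.3–94.3%) | 20/20 = 100% (83.2–100%) | at most 80% |

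These values of k are the expected counts at assumed reaction rates r of 5%, 10% and 20% (20r = 1, 2, 4). The chance that the rule removes at least one of 20 participants is 1 − (1 − r)^20, which is 64%, 88% and 99%.

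**Satisfaction.** Let p be the proportion satisfied among the 20 − k respondents and q the proportion among the k removed. The value for all 20 is ((20 − k)p + kq)/20, so the respondents-only figure is too high by

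p − ((20 − k)p + kq)/20 = (k/20)(p − q).

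| Assumed gap p − q | k = 1 | k = 2 | k = 4 |
|---|---|---|---|
| 25 points | 1.25 | 2.5 | 5 |
| 50 points | 2.5 | 5 | 10 |
| 100 points (upper bound) | 5 | 10 | 20 |

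Entries are percentage points. The gaps are assumptions. Summarising the Likert items as a proportion satisfied is also a simplification made here.

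**The case against.** The strongest reply is that the sentence is only a device safety stop. The article uses study and intervention period loosely: the Outcomes section measures adherence over a six-week study period that is simply the treatment period. The acceptability questionnaire is tied to the end of the intervention and the reminder to the end of the study. For someone who stops early, both could be read as falling at the moment of stopping, with week 6 as the schedule for completers. This stands as a possible reading, so a reader should not infer that the protocol plans to discard these participants' data. It does not say that. But nothing in the article states the looser reading either, and staff will apply the sentence when a participant reports a reaction.

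A second reply is that early-stop procedures are detail which a condensed article leaves to the full protocol. That would answer a complaint about a missing procedure. The point here is about a rule the article does state, whose stated object is the study.

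Thirdly, retention is not defined. If it means completing six weeks of treatment, rewording changes nothing. If it means not being lost to follow-up, someone stopped for a known reaction need not be counted as lost. This stands: a reader might infer that the rule lowers retention on any definition, and that is not supported.

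Fourthly, one might infer that mild redness would trigger removal and that the rule would bite often. The stopping rule speaks of an adverse reaction, while redness and discomfort are listed as adverse events. The article does not equate the two, so frequent triggering is not established.

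Finally, weekly calls and cross-checked diaries record events up to the point of stopping. The count of participants with adverse events is therefore largely preserved, and the reasons for stopping would largely be known. Neither replaces the acceptability questionnaire.

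**Conclusion.** The point holds as a wording defect with a plausible effect on primary outcomes, and it is worth considering at medium confidence. On the literal text, outcome-measure completion is capped at (20 − k)/20, and satisfaction is overstated by (k/20) times the satisfaction gap. Retention shares the cap only if it means remaining under follow-up.

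The real size is unknown, since k and the gap are not in the document. With one or two reactions and a 25-point gap, the overstatement is 1.25 to 2.5 points, small beside the sampling uncertainty at n = 20. It becomes material only with more reactions or a wider gap. If the authors meant stimulation all along, the remedy reduces to saying so.

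**What to change.** Reword the sentence so that an adverse reaction stops stimulation but not study participation, subject to the participant's right to withdraw. For those who stop and are willing:

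- collect the acceptability questionnaire at stopping;
- collect the ICIQ-OAB, King's Health Questionnaire and bladder diary at week 6 as scheduled;
- continue the adverse-event diary and weekly calls to week 6.

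Report stimulation discontinuation due to a reaction separately from loss to follow-up, with everyone sent a device in the denominator. These participants still count as not completing the 6-week intervention. The severity at which stimulation stops remains the investigators' safety decision.

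The cost is one reworded sentence, a minor ethics amendment and modest chasing of people who have stopped. The existing online survey and weekly calls suffice, and the safety stop is untouched.
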